## Abstract

**Background:**

Chronic musculoskeletal pain conditions affect millions of people worldwide and place a significant burden on individuals and the healthcare systems. Managing chronic musculoskeletal pain requires a multidisciplinary approach that considers biological, psychological, and social factors. However, access to multidisciplinary pain care is challenging, and long wait times can lead to increased stress and health deterioration. Mindfulness-based stress reduction (MBSR) is a mind-body approach developed specifically to reduce the distress of living with chronic conditions, such as chronic musculoskeletal pain. This study proposed a novel approach by offering an online MBSR program to patients on waitlists to attend a multidisciplinary pain clinic in Australia’s public healthcare system that could improve health outcomes. The study aims to assess the feasibility, acceptability, and potential efficacy of this approach using a pilot study design with a mixed-methods approach.

**Methods:**

This is a mixed-methods pilot randomised controlled trial with an embedded qualitative study. Participants will be recruited from waitlists at two multidisciplinary pain management centres within the Sydney Local Health District in New South Wales, Australia. This pilot trial will randomly assign 32 individuals with chronic musculoskeletal pain to either an online MBSR group or a usual care control group. Feasibility outcomes, patient-reported outcomes, adherence to mindfulness practice, and adverse events will be assessed using validated questionnaires. Semi-structured interviews will be conducted with participants in the MBSR group to explore their experiences and evaluate acceptability, and barriers and facilitators of engagement with the intervention.

**Discussion:**

This pilot study will evaluate a novel approach to integrating MBSR into the Australian public healthcare system as a mechanism for providing support to individuals with chronic musculoskeletal pain who are waitlisted for a multidisciplinary pain management program. Findings from this study will indicate the feasibility, acceptability, safety, and preliminary efficacy of this approach in terms of patient-reported outcomes to guide the design of future large-scale clinical trials.

**Trial registration:**

This trial was prospectively registered in the Australian New Zealand Clinical Trials Registry (ACTRN12622000822785).

**Supplementary Information:**

The online version contains supplementary material available at 10.1186/s40814-025-01612-w.

## Background

Chronic musculoskeletal pain is a significant public health problem affecting millions worldwide [1], causing widespread suffering for individuals and substantial costs for society [2]. The 2019 Global Burden of Disease (GBD) report illustrates the staggering scale of this problem, reporting that over 1.7 billion individuals worldwide are living with musculoskeletal pain, including neck and lower back pain [3]. Musculoskeletal pain conditions collectively contribute to 149 million years lived with disability (YLD), constituting nearly 17% of the global disease burden. This ranks musculoskeletal pain as the predominant YLD contributor on a global scale [3]. In Australia alone, the financial cost of chronic musculoskeletal pain is estimated at $55 billion annually, incorporating healthcare utilisation, lost productivity, carer burden, and reduced quality of life [4, 5]. Despite treatment advances [6, 7], the prevalence and burden of chronic musculoskeletal pain have increased over time [8], and are expected to continue to increase over the coming decades [9, 10].

Chronic musculoskeletal pain is well-recognised as a multifaceted condition, characterised by a complex interplay of biological, psychological, and social factors, making it challenging to manage [11]. Individuals living with chronic musculoskeletal pain often report high levels of pain-related emotional distress [12–14]. Best practice guidelines recommend integrating physical and psychological interventions for managing chronic pain, often delivered by a multidisciplinary team [15]. This model is an established standard of care provided in public tertiary pain management centres in Australia and is based on specialised assessment and treatment processes, including a multidisciplinary team approach and group pain management programs [16]. However, wait times to access such services often far exceed the recommended 6-month maximum wait, with the most disadvantaged individuals experiencing up to 3 years in the waitlist [17]. Long delays in access to treatment can exacerbate distress and, consequently, physical and psychological deterioration [18]. While system-level strategies are required to reduce waitlist times, we can develop strategies to mitigate the distress and potentially improve the outcomes of patients who are on waitlists.

Mindfulness-based stress reduction (MBSR) is a mind-body training program developed specifically to address the distress associated with long-term conditions, such as chronic pain [19]. The MBSR program combines mindfulness meditation, body awareness, yoga, and exploration of patterns of behaviour, thinking, feeling and action [20]. By engaging participants holistically on multiple levels (i.e. physiological and emotional regulation, cognitive reappraisal, behavioural change, engagement with values, and social connection), MBSR has been shown to significantly reduce pain [21, 22], improve symptoms of anxiety, and depression and improve quality of life, in people with various chronic conditions [23], including chronic musculoskeletal pain [22–24]. MBSR is typically delivered as a face-to-face, 8-week program, with weekly 2.5-h group sessions, and an expectation of daily practice by participants [20]. However, recent evidence has shown that online delivery of MBSR is comparably effective to in-person delivery [25]. An online delivery mode allows participants to complete the program without the need to travel to a single location, which can pose logistical and financial challenges [26].

Despite evidence supporting the efficacy of MBSR in improving patient-reported outcomes for chronic pain [21], availability to patients in Australia remains limited. MBSR programs are primarily offered as privately funded courses, which are costly thereby excluding a large proportion of patients with chronic musculoskeletal who cannot afford it [27]. Addressing this barrier to access calls for the incorporation of MBSR programs into the public health system [28]. This shift could improve access to a mind-body approach that can improve the well-being of patients with chronic musculoskeletal pain, thereby mitigating health inequities. However, implementing a novel intervention in health services requires significant and planned changes, and the first step is to test its practicality [29]. In this context, pilot studies play a crucial role in testing and refining the research methods and procedures prior to a fully powered clinical trial. Pilot trials further assist in identifying potential barriers and facilitators related to the intervention, enable assessment of the feasibility of data collection and analysis, and by uncovering any issues early on, guide necessary adjustments that improve the quality and efficiency of fully powered clinical trials [30].

Our study, therefore, aims to (1) evaluate the feasibility of an online MBSR program for managing chronic musculoskeletal pain within the public health care system in Australia; (2) identify barriers and facilitators related to the online MBSR program for people with chronic musculoskeletal pain; and (3) determine the preliminary efficacy and safety of the online MBSR program compared to usual care on patient-reported outcomes.

## Methods

### Study design

This is a pilot randomised controlled trial (RCT) with an embedded qualitative study. We will follow the first two steps in the Sax Institute’s Translational Research Framework [31] to investigate the feasibility and preliminary efficacy of an online MBSR program for chronic musculoskeletal pain. This Translational Research Framework serves to bridge the gap between research and real-world implementation by systematically addressing barriers at different stages of translation. This study specifically focuses on two key translational steps: (1) T1 (feasibility testing): assessing the feasibility of the intervention in a controlled setting, including recruitment, adherence, and preliminary engagement outcomes; and (2) T2 (clinical research): assessing the preliminary efficacy of the intervention to determine its potential benefits. These steps provide a structured approach to evaluating the feasibility and preliminary efficacy of the online MBSR program for individuals with chronic musculoskeletal pain [32].

This study employs an exploratory sequential mixed-methods design, in which quantitative data will be collected first, followed by qualitative interviews to provide further insights into participants’ experiences. This approach enables the identification of key trends in the quantitative data, which can then be explored in greater depth through qualitative methods. The quantitative component will assess recruitment rates, intervention adherence, patient-reported outcomes, and adverse events, providing objective feasibility data. The qualitative component, gathered through semi-structured interviews, will explore participants’ experiences with the program, including barriers and facilitators to engagement, intervention acceptability (e.g. content, complexity, delivery, and areas for improvement), and key factors influencing future implementation and scalability. This integrated approach ensures a comprehensive evaluation of both feasibility and user experience, informing the design of a larger-scale trial. To ensure clarity and transparency in reporting, study findings will adhere to the CONSORT 2010 statement: extension to randomised pilot and feasibility trials [33]. The qualitative component will be reported following the Consolidated Criteria for Reporting Qualitative Research (COREQ): a 32-item checklist for interviews and focus groups [34].

### Participants’ inclusion and exclusion criteria

#### Pilot RCT

A total of 32 individuals with chronic musculoskeletal pain will be randomised to either an online MBSR group (*n* = 16) or a usual care control group (*n*= 16). This sample size has been determined based on feasibility considerations and recommendations for pilot studies. A detailed justification is provided in the Sample Size section (page 16). We will include people that (i) are 18 years or older; (ii) have chronic primary or secondary musculoskeletal pain as described by the IASP (International Association for the Study of Pain) classification of chronic pain for ICD-11 (i.e. “pain located in the muscles, bones, joints, or tendons”) [35]; (iii) are proficient in English (i.e. able to read and understand the consent form, participant information sheet, and study materials without the need for assistance from a translator); (iv) are able to access the internet via a computer (desktop or laptop) or a smartphone. We will exclude people who (i) have pain from serious pathologies such as fractures or cancer; (ii) have self-reported active or uncontrolled mental illness (i.e. severe depression, active suicidality, bipolar disorder, and schizophrenia that is not managed by a health care professional—psychologist, psychotherapist, psychiatrist); (iii) have a history of an unexplored, untreated traumatic experience or adverse childhood events assessed by an experienced clinician during the telephone screening process; or (iv) are judged at the investigator’s discretion as being unsuitable to participate (e.g. inability or unwillingness to attend the weekly group sessions).

#### Qualitative study

Participants from the intervention group (MBSR group) participating in the pilot RCT will also be invited to participate in the embedded qualitative study, which will use in-depth semi-structured interviews to explore the participant’s experience in the MBSR program. We will strive to recruit a diverse sample of participants covering a broad population, including people from varied occupation status and cultural backgrounds, age groups, and genders.

### Recruitment

#### Pilot RCT

##### Pre-screening

We will recruit individuals with chronic musculoskeletal pain who are on the waitlist to receive care at the pain management centres at Royal Prince Alfred Hospital (RPAH) and the Concord Repatriation General Hospital (CRGH) in the Sydney Local Health District (SLHD) in Sydney, New South Wales (NSW), Australia. The average time spent on the waiting list to access the Pain Management Centre at RPAH and CRGH varies from 6 to 12 months.

The Clinical Nurse Consultants at the RPAH and CRGH pain management centres will call individuals on the waitlists and inform them about the study. They have received training in describing the study and answering questions related to the study protocol from the Coordinating Principal Investigator. The Clinical Nurse Consultants have also been provided with a script to use during the telephone calls. If individuals are interested in learning more about the study, the Clinical Nurse Consultants will ask permission to (a) share their name and contact information with the research team; and (b) send them an email containing a study advertisement and a Participant Information Sheet that describes the study’s eligibility pre-screening process. The recruitment email also contains a link that will take them to a pre-screening Consent Form and a short pre-screener survey created with the Research Electronic Data Capture (REDCap), which will contain some questions regarding their eligibility for joining the study. Where permission is given, after each phone call, the Clinical Nurse Consultants will share the name, phone number and email address of the interested potential participants with the research team, via a form on REDCap.

If a potential participant does not answer the Clinical Nurse Consultant’s phone call, they will be sent an SMS that will inform them about the study. The SMS will contain a URL link that will take them to an online copy of the Participant Information Sheet, the pre-screening Consent Form, and the short pre-screener survey. The SMS will be sent using a programmable messaging API (Application Programming Interface) from Twilio that is integrated with REDCap. Potential participants can reply ‘STOP’ to the SMS to opt out of any future communications about the study.

Potential participants who expressed interest in the study over the phone with one of the Clinical Nurse Consultants who did not complete the pre-screener survey will be sent a reminder email 3 to 5 days after the initial email. The reminder email will also mention that a research investigator may contact potential participants on their provided phone number to see if they have received this email and if they are still interested in learning more about the study.

If potential participants do not complete the pre-screener survey after the reminder email, a research investigator will call them 1 week after the initial contact from the Clinical Nurse Consultants to ask if they have received the email and if they are still interested in learning more about the study. This will be the last attempt to contact the participants. No further contact will be made if they are not interested. During the call, if they remain interested in the study, the research investigator will direct the potential participants to the email or re-send the email with the Participant Information Sheet, Consent Form and the pre-screener survey. Potential participants will also have the opportunity to ask questions about the study during the phone call.

If a potential participant who received a recruitment SMS and did not opt out of future communications about the study does not complete the pre-screener survey, they will be sent a follow-up SMS 5 days after the initial SMS. This will be the last attempt to contact the participants. No further contact will be made if they are not interested.

If eligible after completing the pre-screener survey, potential participants will receive a phone call from an experienced MBSR teacher and psychotherapist to screen for mental health concerns. During the phone call, the MBSR teacher will ask eleven questions to screen for any severe and uncontrolled mental health condition or a history of an unexplored, untreated traumatic experience. If eligible after completing the mental health screen, potential participants will be reminded that if they agree to participate in the study, they have a 50% chance of being in either the MBSR group or the usual care control group.

Participants in the usual care group will continue to receive the care that patients usually receive while they are on the waitlist to attend the pain management centres at the RPAH and CRGH. Potential participants will also be asked their preferred day and time to attend the weekly 2.5-h MBSR group sessions, in case they agree to enrol in the study and are allocated to the MBSR group. If ineligible, individuals will be provided with the reason why they are not eligible for the study. All ineligible individuals will be given the contact details of the Coordinating Principal Investigator, who can clarify any questions they may have. They will be informed they will remain on the waitlist to receive care at the RPAH or the CRGH pain management centres. If individuals are distressed because they are ineligible for the study, they will be referred to the Pain Specialist and Site Principal Investigator from the relevant Pain Management Centre, or if unavailable, the relevant Clinical Nurse Consultant, for support. If necessary, the Clinical Nurse Consultant will refer the participant to the Clinical Psychologist available on the day.

### Enrolment

Potential participants who are deemed eligible to join the pilot RCT after the pre-screening process, and who indicate an interest in participating in the pilot RCT, will be sent the pilot RCT Participant Information Sheet via email to keep. Potential participants can take their time to think and decide. If they agree to join the RCT, they will be asked to sign a consent form embedded into REDCap. A link to the consent form will be sent via email. Potential participants who do not complete the electronic consent form will be sent a follow-up email 3 to 5 days after the initial email. The reminder email will also mention that a research investigator may contact potential participants on their provided phone number to check receipt of this email and confirm that they are still interested in participating in the study. If a potential participant does not complete the electronic consent form after the follow-up email, a research investigator will call them 1 week after the initial email to determine whether they have received the email and whether they are still interested in participating in the study. This will be the last attempt to contact the participants. The screening process is illustrated in the screening flowchart (Fig. 1). Should participants volunteer, the research investigator will emphasise that they are free to withdraw from the study at any time without penalty.

**Fig. 1 Fig1:**
[figure not shown]
Screening flowchart

Group allocation

After eligibility is confirmed, participants will be randomly assigned to either the online MBSR intervention or the control group using a computer-generated randomisation sequence with a 1:1 allocation ratio. An independent researcher not involved in recruitment will generate the randomisation sequence to minimise bias. Randomisation will occur after baseline data collection to prevent allocation bias.

#### Qualitative study

All participants completing the MBSR program as part of the pilot RCT will be purposively invited for in-depth interviews after completing the program. Research investigators will contact MBSR program participants to invite them to take part in the interviews after the program is finished. Potential participants interested in participating in the interviews will receive the Participant Information Sheet and Consent Form via email.

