### Sample size

#### Pilot RCT

Decisions about sample size in pilot studies can be challenging as a variety of approaches exist [49–52]. Some researchers suggest that pilot studies should include at least 30 participants to provide a reliable estimate of the standard deviation, which is essential for calculating the sample size of a future full-scale trial [51]. Based on these guidelines, we plan to recruit 32 participants (approximately 16 per group) for this pilot study. This represents 9% of the estimated sample size for the full trial, which is the minimum threshold recommended by Cocks and Torgerson (2013) [50]. This sample size provides >80% confidence in determining whether to proceed with a full trial, aligning with feasibility objectives. The calculation is based on an estimated effect size difference for the full trial, using a confidence interval approach [50]. A key feasibility outcome is the retention rate, which we anticipate to be 80%. Given our sample size (*N*= 32), this can be estimated to be within approximately ±15% with 95% confidence, meaning that around 26 participants are expected to complete the study [39]. However, we acknowledge that this estimate is provisional and will be refined based on feasibility data collected from the pilot study, including actual retention rates, standard deviation estimates, and adherence metrics.

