#### Qualitative study

In qualitative research, the sample size needs to enable rich and diverse data to be collected to provide valuable insights about the topic of interest and to be sufficient to generate an in-depth understanding of it [53]. Based on this information, we have estimated that around 12 to 15 participants may be necessary to reach the qualitative purposes of this study.

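### The enrolment text invites only MBSR completers to interview while other sections invite the MBSR group; followed literally, it leaves early leavers out of the evidence on barriers and acceptability.

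*Protocol article*

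**What the plan says.** Four places in the protocol article describe who is interviewed.

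- Abstract, Methods: "Semi-structured interviews will be conducted with participants in the MBSR group".
- Participants' inclusion and exclusion criteria, Qualitative study: "Participants from the intervention group (MBSR group) participating in the pilot RCT will also be invited to participate in the embedded qualitative study".
- Enrolment, Qualitative study, first sentence: "All participants completing the MBSR program as part of the pilot RCT will be purposively invited for in-depth interviews after completing the program".
- Enrolment, Qualitative study, second sentence: "Research investigators will contact MBSR program participants to invite them to take part in the interviews after the program is finished".

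Only the third makes completion a condition. The text shown does not define programme completion, and no sentence expressly includes or excludes those who stop early.

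The interviews serve the second aim at the end of the Background: "identify barriers and facilitators related to the online MBSR program for people with chronic musculoskeletal pain". The Study design section and the section on acceptability, barriers and facilitators make interviews the means of studying engagement and acceptability. The Data analysis section combines the interview findings with the quantitative results, adherence among them.

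On numbers, the Sample size section says "we plan to recruit 32 participants (approximately 16 per group) for this pilot study" and, for the interviews, "we have estimated that around 12 to 15 participants may be necessary to reach the qualitative purposes of this study". Separately, the Feasibility outcomes section says that reasons for dropping out will be recorded.

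**The concern.** An interview study of barriers to engagement learns most from a sample that includes people for whom a barrier was decisive. A completion condition removes them from the sample. The article expects some of them: it anticipates 80% retention, it notes under Study limitations that digital programmes often lose more participants, and it says under Adverse events that a distressed participant may be advised to stop the intervention. Under the literal enrolment sentence, that last person would not be asked in interview about acceptability.

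The interviews are meant to explain adherence and to shape the larger trial, so a sample selected on completion could carry its selection into that design. As the text stands, staff who follow the enrolment sentence and staff who follow the participants section would invite different people.

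A second, smaller worry is yield. The interview target is close to the number of people likely to complete one arm of 16.

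**Working it through.** **Comparing the passages.** Three descriptions (abstract, participants section, second enrolment sentence) set no completion condition. One (first enrolment sentence) does, and it also times the invitation after completion. The narrow sentence sits in the section that governs recruitment to the interviews, so it cannot be dismissed as a summary. The sentence directly after it is broader, so the narrow reading is not settled either. The text does not resolve the difference.

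**Inputs.** From the article: 32 randomised, about 16 per arm; anticipated retention 80%; interview target around 12 to 15; amber progression level 60% retention. Not in the article: the MBSR completion rate and the proportion of invited people who agree to be interviewed. Both are assumptions below.

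**The article's own figure.** 32 × 0.80 = 25.6, which rounds to the stated 26 or so. The 95% half-width is 1.96 × √(0.8 × 0.2 / 32) = 0.139, or 13.9 points, consistent with the stated approximate ±15%. The retention arithmetic reproduces.

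**MBSR arm, if 80% is taken as the completion rate.**

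- Expected completers: 16 × 0.80 = 12.8.
- Expected early leavers: 16 − 12.8 = 3.2, or about 3.
- Share of expected completers needed for 12 interviews: 12 / 12.8 = 94%.
- For 15 interviews: 15 / 12.8 = 117%.
- Share of the whole arm needed: 12 / 16 = 75% to 15 / 16 = 94%.

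**Chance of reaching the target from completers only.** Take the number of interviews as binomial with n = 16 and probability completion × uptake.

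| Completion | Uptake (assumed) | Expected interviews | P(at least 12) | P(at least 15) |
|---|---|---|---|---|
| 90% | 100% | 14.4 | 0.98 | 0.51 |
| 80% | 100% | 12.8 | 0.80 | 0.14 |
| 80% | 90% | 11.5 | 0.52 | 0.04 |
| 80% | 80% | 10.2 | 0.26 | 0.01 |
| 60% | 100% | 9.6 | 0.17 | 0.003 |

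**If all 16 are invited.** With 90% uptake, P(at least 12) = 0.98. With 80% uptake it is 0.80. These figures assume that early leavers agree as often as completers, which may be optimistic.

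**The case against.** The strongest reply is that nothing in the article excludes early leavers. Three of the four descriptions are broad, completion is undefined, and the first enrolment sentence may be loose drafting. This stands in part. A reader might infer that early leavers are excluded by rule and that only completers will be interviewed; the documents do not settle that. They give an inconsistency, and one side of it carries the risk.

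Next, those who stop are not unobserved. Drop-out reasons are recorded, a lessons-learned document is kept, and practice adherence and adverse effects are collected weekly, so some data may precede the stop. Completers can also report barriers of time, technology, content or delivery. This too stands: it would be too strong to say that barriers are studied only in people who overcame them, or that acceptability will be overstated. It does not remove the point, because a recorded reason is not the in-depth account that the article itself treats as essential.

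A reader might also infer from 12.8 against 12 to 15 that the plan's numbers conflict. They do not. The 80% is study retention over both arms, and a person may stop MBSR yet stay in the study. The target is hedged as approximate, and 12.8 lies inside it. Every probability below full uptake rests on an assumed uptake.

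Finally, inviting all 16 does not create room for purposive or diverse selection. That limit comes from the size of the arm, not from the completion condition.

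**Conclusion.** The point holds as an inconsistency with a selection risk. The article states two sampling frames for the same interviews, and the narrower one, if followed, omits the people most likely to have met a decisive barrier. This affects one of the three stated aims. It does not touch the randomised comparison or the retention criterion.

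The number omitted would be about 3 of 16 if overall retention is a fair guide to MBSR completion; the article does not say that it is. The direction and magnitude of any bias in the themes cannot be calculated from the article.

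The yield argument is secondary and depends on assumptions. A completer-only pool leaves little margin: a 0.80 chance of at least 12 interviews if everyone agrees, and less with any refusals.

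**What to change.** Reconcile the abstract, the participants section and the enrolment section on one frame. Suggested replacement for the first enrolment sentence: *Everyone randomised to MBSR, including those who stop attending or withdraw from the programme and still agree to be contacted, will be invited to a voluntary interview after the programme period.* Holding the interviews after the programme period keeps the quantitative-then-qualitative order in the Study design section.

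Also define programme completion, so that completers and early leavers can be told apart in the report, and state the target of around 12 to 15 against the arm of 16 with an assumed uptake.

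The cost is about 3 extra invitations under the 80% assumption and a line in the consent form. The interview information sheet and consent form are not shown, so the exact change there cannot be judged. Because some people may have stopped on account of distress, the invitation must rest on their continuing agreement to contact.
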